**Figure 1 figure1:**
[figure not shown]
Timeline of study activities. AP: anchoring plan; BM: self-monitoring behavior; NTCI: non–time-contingent incentive; OM: self-monitoring outcomes; TCI: time-contingent incentive; UC: usual Calm.

### Sample Size

The target recruitment sample size for this study is 555 participants, with 111 participants per study group. On the basis of our existing studies using the Calm app, we anticipate a 20% study attrition, which will yield an effective study group sample size of 88. Our primary measure of meditation app adherence is a binary indicator variable for performing ≥10 minutes of meditation on at least 4 days of the week. This measure of adherence is based on the concept of behavioral regularity, which was proposed by Cheung et al [102] as a standardized measure of treatment adherence. In addition, researchers have recommended that practicing mindfulness for 3 to 4 days per week is the sufficient level of adherence (or regularity) for attaining the mental health benefits associated with meditation, such as stress reductions [103], and this recommendation is theoretically consistent with the notion that a mindful mind is the product of frequent, effortful, and persistent training [104,105]. Thus, we determined our sample size to detect study group differences in meditation regularity at the end of the study (week 16). Using data from our previous studies with Calm, we know that approximately 15% of new Calm users regularly meditate (ie, complete ≥10 minutes of meditation for at least 4 days of the week) 8 weeks after first subscribing to the app and fewer than 10% regularly meditate with Calm 16 weeks after subscribing. An effective study group sample size of 88 provides adequate statistical power (1–β=.82) for detecting study group differences of 18 percentage points in the likelihood of regular mediation in week 16 (Cohen *h*=0.43, which is a small to medium effect size).

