#### Primary Outcomes: Adherence Maintenance (Objective App Use Data)

The primary outcomes for this study measure participants’ ability to maintain adherence to the ≥10 minute-per-day meditation prescription over the 16-week study period. Specifically, we will measure meditation adherence as a binary variable equal to 1 if participants complete ≥10 minutes of meditation for ≥4 days per week and 0 otherwise. This meditation adherence outcome will be defined weekly during both the 8-week intervention and the 8-week postintervention observation periods. We will also measure objective meditation app use using the number of days with ≥10 minutes of meditation per week and the total number of meditation minutes per week, both of which will allow us to investigate the behavioral frequency of app-based meditation and improve the statistical power of our analyses. We will also augment these objective app-based meditation measures with a self-reported measure of days with any meditation (ie, either using the app or meditation outside the app) over the past week that is assessed at baseline, week 8, and week 16 time points. We will measure anchoring plan adherence as a binary variable equal to 1 if participants complete ≥10 minutes of meditation within 1 hour of the timing of their chosen anchor for ≥4 days per week and 0 otherwise. Similar to overall meditation, we will also measure anchoring plan adherence as the number of days completing ≥10 minutes of meditation within 1 hour of the timing of their chosen anchor per week.

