#### Satisfaction

Participant satisfaction will be assessed at weeks 8 and 16. All participants will be asked to rate their overall enjoyment and satisfaction with the Calm app and the study itself, as well as their intent to continue using the app along with the app features (eg, mood tracking and session tracking) and app content (eg, daily meditations, sleep meditations, and soundscapes) that they found most helpful for maintaining their daily meditation practice. Then, participants will be asked specific questions regarding their chosen meditation anchor, such as how easy it was to select and use their chosen anchor during the intervention, their intent to continue using their meditation anchor, and the helpfulness of the anchoring plan in maintaining their meditation practice. Participants in the intervention groups will also be asked questions related to the incentives, including how easy it was to understand the incentive process; how easy it was to earn incentives; if they liked the incentive options, how motivated they were by the incentives; and if there was anything that would have motivated them more. This information will provide helpful qualitative data that can be used to improve future adherence studies, including the types of anchoring strategies that are most successful in establishing a meditation habit and what motivates people to establish and maintain an app-based meditation habit.

Attrition will be assessed at all stages of the study: (1) enrolled but did not complete the baseline assessment, (2) completed baseline assessment but lost to follow-up during the 8-week intervention period (ie, did not complete week 8 assessment), and (3) completed the 8-week assessment but lost to follow-up during the 8-week postintervention observation period (ie, did not complete the week 16 assessment).

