#### Introductory Video

Immediately following the web-based surveys, participants will then watch 1 of 3 brief 5-minute introductory videos that will vary slightly based on their experimental conditions. All 3 videos will contain background information on the benefits of mindfulness meditation and habit formation (eg, previous research and theory); a sample anchoring plan (eg, “After [insert behavior here], I will meditate for 10 minutes”); a study timeline (ie, baseline assessment, 8-week intervention period, follow-up assessment, 8-week postintervention period, and second follow-up assessment); and compensation information for completing the 3 web-based surveys (US $20 gift card). In addition to these foundation elements, participants in the NTCI and TCI groups will be told in the video that they are eligible for incentives every 2 weeks during the 8-week intervention period conditional on either meditating at any time (NTCIs) or meditating using their anchoring plan (TCIs). The video for the usual Calm condition will only include the foundation elements mentioned previously, with no mention of incentives or personalized feedback messages. Information in all 3 videos will be presented by a member of the study team using both written and spoken texts. Participants in the NTCI and TCI groups will also receive instructions regarding prize eligibility as detailed in the *Study Design* section.

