#### Anchoring Plan Worksheet

After watching the introductory video, participants will complete a video comprehension quiz to ensure that they understand the study timeline and requirements. Participants must score 100% on the quiz to move on with the study. Then, all participants will be asked to complete a web-based worksheet to help them develop a meditation anchoring plan. This worksheet will first ask participants to fill out a basic implementation intention plan (ie, “After _____, I will meditate for 10 minutes”) based around a routine behavior (ie, their anchor) they perform in the morning, given that previous research suggests the morning habits are easiest to form [31]. Next, participants will be instructed to add additional details to their anchoring plan to make it more specific (eg, anchor timing and anchor location), as generic plans may not be as effective as plans that specifically outline when and where this behavior will occur. After finalizing their anchoring plan, the participants will be emailed a copy of their anchoring plan for their records.

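### Randomisation comes before the baseline survey, arm-specific video, quiz and anchor worksheet, so participants who stop there have no defined outcome weeks, and anchor times are set with different knowledge by arm

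*Protocol article*

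**What the plan says.** Under Recruitment and Enrollment Procedures, participants are randomised once they have consented, while they wait for the emailed baseline survey. Study Design and Randomization and Baseline confirm that the survey follows randomisation. Next, under Introductory Video, "participants will then watch 1 of 3 brief 5-minute introductory videos that will vary slightly based on their experimental conditions"; the two incentive versions explain what earns a prize and the third does not mention incentives. Anchoring Plan Worksheet adds a quiz: "Participants must score 100% on the quiz to move on with the study". The participant then chooses an anchor and its timing. Intervention, Postintervention, and Follow-up Surveys starts the 8-week period only when the baseline assessment and worksheet are complete.

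Both primary outcomes come from app records. Weekly meditation adherence is "equal to 1 if participants complete ≥10 minutes of meditation for ≥4 days per week and 0 otherwise". Anchoring plan adherence also requires the session to fall within 1 hour of the chosen anchor's timing. The adjusted model in the Data Analysis Plan includes baseline meditation habit strength, which is collected in the baseline survey.

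Under Sample Size, "The target recruitment sample size for this study is 555 participants, with 111 participants per study group", and "we anticipate a 20% study attrition, which will yield an effective study group sample size of 88". The Satisfaction section tracks attrition by assessment completion: first, enrolled without completing baseline; then, "completed baseline assessment but lost to follow-up during the 8-week intervention period (ie, did not complete week 8 assessment"); and last, the same for week 16.

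**The concern.** Randomisation makes the groups comparable at the moment of allocation. Here four steps lie between allocation and the first study week, and one of them, the video with the quiz on it, differs by arm. Anyone who stops in between has been randomised but has no position on the study clock. If these people drop out of the analysis, the comparison is restricted to those who got through, and getting through is plausibly related to later app use, which is what the trial measures.

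The second matter is the anchor time. It is part of the definition of a primary outcome, yet it is set after the arms have been told different things. A time-contingent participant has a reason to pick a time that is easy to hit. A non-time-contingent or control participant does not have that reason. Hypothesis 2 compares the two incentive types on exactly this outcome. A difference could therefore reflect which times were chosen as well as how well the plan was followed.

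**Working it through.** **1. What is defined for a randomised participant who stops early.**

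| Stops before finishing | Start of week 1 | Anchor time | Baseline habit strength |
|---|---|---|---|
| Baseline questionnaires | undefined | none | missing |
| Video or quiz | undefined | none | recorded |
| Anchor worksheet | undefined | none | recorded |
| Nothing (all steps done) | defined | recorded | recorded |

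The app log exists for everyone, but without a start date it cannot be cut into weeks 8 and 16. Coding no use as 0 does not help until the week is defined. Anchoring adherence cannot be scored without an anchor time. An ordinary logistic fit of the adjusted model also drops anyone whose baseline covariate is missing, unless it is imputed.

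**2. Where loss could depend on arm.** The wait for the email and the questionnaires come before any arm-specific information, so loss there cannot be a response to the allocation. The worksheet is the same for all arms, though it follows the disclosure. The steps with arm-specific content are the video and, possibly, its quiz.

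**3. The plan's own power figure.** Inputs from Sample Size: 111 per group, 20% attrition, h = 0.43, power 0.82. Two-sided alpha of 0.05 is assumed, as the article gives none.

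- 111 × 0.80 = 88.8, given as 88.
- Power = Φ(h√(n/2) − 1.96) = Φ(0.43 × √44 − 1.96) = 0.814.
- Two-proportion formula, 15% against 33%, n = 88: 0.804.

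The stated 0.82 is reproduced to within 2 points.

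**4. Size of a selection effect, by assumption.** Let the true rate p be equal in both arms, and let only non-adherers be lost, a fraction d. The rate among those left is p/(1 − d).

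| True rate, both arms | Loss by arm | Observed rates | Spurious difference |
|---|---|---|---|
| 15% | 20% / 20% | 18.75% / 18.75% | 0 |
| 15% | 15% / 25% | 17.6% / 20.0% | 2.4 points |
| 15% | 10% / 30% | 16.7% / 21.4% | 4.8 points |
| 10% | 15% / 25% | 11.8% / 13.3% | 1.6 points |
| 10% | 10% / 30% | 11.1% / 14.3% | 3.2 points |

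Equal loss raises both rates but creates no difference.

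**5. Does analysing all 111 raise power?** Holding 15% against 33% fixed, n = 111 gives 0.886 (0.893 by h = 0.43). That treats the lost participants as no different from the rest. Under the assumption in step 4, that they are non-adherent, with 20% loss in each arm:

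- If the planning rates describe completers, all randomised have 0.8 × 15% = 12.0% and 0.8 × 33% = 26.4%. Power at n = 111 is 0.781, against 0.804 for completers at n = 88.
- If the planning rates describe all randomised, completers have 15/0.8 = 18.75% and 33/0.8 = 41.25%. Power at n = 88 is 0.91, against 0.886 at n = 111.

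Either way, no power is gained.

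**The case against.** The strongest reply is that nothing in the article removes anyone from the analysis of app data. The 20% is a planning allowance, the list of attrition stages is a tracking statement, and the analysis plan sits in an appendix that is not shown. This stands. A reader might infer from the effective size of 88 that survey non-completers are to be dropped; the documents do not say so. Some allowance is reasonable even for app data, since participants may ask for their data to be removed.

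It is also fair that the videos are said to vary only slightly, that the article does not say whether the quiz may be retaken, and that no loss rate by arm is given. Arm-dependent loss is therefore a risk that the sequence creates, not a documented event.

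On the anchor, every arm is steered to a morning routine, and knowing that prizes depend on timing is part of the time-contingent strategy. The first narrows the room for strategic choice without removing it. The second justifies telling participants about the prizes, but not telling them before the outcome's reference time is fixed.

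The reply does not reach the undefined weeks. Those follow from the article's own order of events and its own rule for starting the clock, and a statement of the analysis set would not by itself supply a start date or an anchor time.

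**Conclusion.** The point holds as a weakness of sequence. Randomised participants who do not finish the baseline steps have no defined outcome weeks and no anchor time, and the anchor time is chosen with different knowledge in different arms. The consequences are possible post-randomisation selection, which could differ by arm at the video and quiz step, and an anchoring outcome that may not be comparable between incentive types.

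The size is unknown. Under the assumed losses above, spurious differences run from 1.6 to 4.8 points. That is small beside the planned "study group differences of 18 percentage points in the likelihood of regular mediation in week 16", but it arises with no true effect. The figures rest on losing only non-adherers and on unequal loss; with equal loss there is no difference.

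Two stronger readings are not supported. The plan does not state that survey non-completers are excluded. Nor can it be said that analysing all 111 would lift power to 0.89, because under the same assumption about dropouts it does not. The statement "An effective study group sample size of 88 provides adequate statistical power" reproduces, and 88 per group may stay as a conservative planning figure.

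**What to change.** 1. Change the order. Run the baseline survey, a common foundation video, the quiz and the anchor worksheet first; then randomise; then show the segment on incentives. Every randomised participant then has an anchor time, a start date and baseline covariates, and all arms choose the anchor with the same knowledge. The cost is splitting the video and randomising, stratified as now, inside the web survey instead of in a batch.

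2. State that the app-based primary outcomes are analysed in all randomised participants regardless of week-8 or week-16 survey completion, except those who ask for their data to be removed, with no qualifying use coded 0. This costs wording only.

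3. Recruitment was expected between March and May 2022, so the order may no longer be open to change. In that case, start the clock for meditation adherence at a date that does not depend on completing baseline. The cost is that study weeks line up less exactly with the delivered intervention. This does not rescue anchoring adherence, which still needs an anchor time; report that comparison as conditional on a completed worksheet, with the number per arm who stopped at each baseline step.

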### Eligibility

Participants will be eligible and included in our sample if they are aged at least 18 years, are new Calm subscribers (ie, have purchased at least 1-year of membership within the past week), are able to read and understand English, have access to a smartphone daily, reside in the United States or a US territory, and have a Perceived Stress Scale (PSS; PSS-4) score ≥6. Participants will be excluded if they are new Calm subscribers but have used Calm for ≥2 days in the last week, have practiced meditation (including meditative movement, ie, yoga or tai chi) for >60 minutes a month in the past 6 months, or are unable to provide consent or understand study procedures owing to mental illness or cognitive limitations.

### Recruitment and Enrollment Procedures

Potential participants will be invited to participate in the study via weekly recruitment emails sent by Calm to all new subscribers. The recruitment email will contain a link to complete an eligibility survey using the survey software Qualtrics (Qualtrics International Inc). Recruitment emails will be sent every week for 6 consecutive weeks or until the target sample size has been met. Participation will be voluntary, and participants may withdraw from the study at any time.

The eligibility survey will contain a brief overview of the study along with a series of questions based on the eligibility criteria listed in the previous section. If eligible, the participants will be asked to read an electronic consent form and provide their consent via electronic signatures. The electronic consent form also contains 2 comprehension questions to ensure that participants understand the study procedures. Once consented and enrolled, participants will be told that they will receive additional study instructions (ie, the baseline survey) via email in the coming weeks. During this time, eligible participants will be randomized based on the stratification dimensions described in the *Study Design* section.

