Despite these promising findings, the efficacy and generalizability of app-based interventions are limited by their substantial attrition and poor adherence. Previous meta-analyses have estimated app-based intervention study attrition rates to range from 31% to 42% and intervention adherence rates (ie, the number of sessions actually completed compared with the prescribed amount) to range from 39% to 92% [15,16,30]. Baumel et al [17] examined objective user adherence with various mental health Android apps, including those specifically for mindfulness meditation, and found that only a small portion of users actually used the apps for an extended period, with open rates declining >80% between days 1 and 30 across all mental health apps. For mindfulness meditation apps specifically, median 15- and 30-day retention rates were 4.9% and 4.7%, respectively [17], greatly limiting the efficacy of these mHealth tools. Similar patterns of declining adherence have been observed in our research with the Calm meditation app, in which adherence rates to the daily prescription of ≥10 minutes of meditation with Calm fell by approximately 68% over the course of a 16-week study period [31]. This pattern of rapidly declining meditation app use limits the impact of these mental health solutions. The next step in the mHealth research is therefore to find effective interventions to keep mobile app users engaged, that is, to maintain meditation app adherence.

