#### Intervention, Postintervention, and Follow-up Surveys

The 8-week intervention period will begin once the participants complete the baseline assessment and anchoring plan worksheet. All the participants will be asked to meditate for ≥10 minutes every day during the intervention period. Every 2 weeks, participant use data will be checked to determine incentive eligibility for participants in the NTCI and TCI groups. Every week, all the participants will also receive a text message from the study team as a reminder to continue meditating using their chosen anchor. In addition, participants in the BM group will receive a message focused on self-monitoring of their meditation behavior every 2 weeks that informs participants of the number of ≥10-minute meditations they completed during the past 2 weeks. Participants in the self-monitoring of outcomes of behavior messages groups will receive a message focused on self-monitoring of outcomes of their meditation behavior (ie, mood tracking) every 2 weeks that encourages the participants to keep track of their mood using the “How Are You Feeling?” feature in the Calm app. After 8 weeks, participants will be emailed a link to complete the first of the 2 follow-up surveys. These surveys will assess any improvements in the secondary outcome measures assessed at baseline, as well as their satisfaction with both the Calm app itself and the interventions. Following the completion of the 8-week intervention period and the week-8 follow-up survey, participants will be asked to continue using their anchors to strengthen their meditation habits during the 8-week postintervention observation period. However, unlike in the intervention period, participants in all intervention groups will no longer receive weekly reminders, biweekly self-monitoring messages, or incentives during the postintervention period. Participants will then be contacted at week 16 to complete the second follow-up survey to assess changes in the secondary outcome measures at week 16.

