where *y_i_* is a binary variable equal to 1 if individual i completed ≥10 minutes of meditation for ≥4 days during week 8 of the study; T1 is an indicator for treatment group 1 (that receives self-monitoring behavior messages and NTCIs); T2 is an indicator for treatment group 2 (that receives self-monitoring outcome messages and NTCIs); T3 is an indicator for treatment group 3 (that receives self-monitoring behavior messages and TCIs); T4 is an indicator for treatment group 4 (that receives self-monitoring outcome messages and TCIs); and *ϵ_i_* is the idiosyncratic error. The coefficients of interest are *β*_1_ through *β*_2_. Equation 2 has the term *X_i_β*_5_, which includes a vector of the following observable participant characteristics (*X_i_*): age, education, sex, race, ethnicity, household income, self-reported mental and physical health, baseline meditation habit strength, intrinsic motivation for meditation, and measures of time and risk preferences and the respective coefficients (*β*_5_). For more information on our data analysis plan, please see Multimedia Appendix 1.

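### Meditation practice during the open-ended wait between screening and week 1 is left out of the primary model, which costs precision but not validity

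*Protocol article*

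**What the plan says.** Under Eligibility, participants must "have purchased at least 1-year of membership within the past week" and are excluded if they "have used Calm for ≥2 days in the last week". Both conditions are checked in the web-based eligibility survey.

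Under Recruitment and Enrollment Procedures, once consent is given, "participants will be told that they will receive additional study instructions (ie, the baseline survey) via email in the coming weeks". Randomisation takes place during this interval. The same section says: "Recruitment emails will be sent every week for 6 consecutive weeks or until the target sample size has been met". That limits the recruitment campaign, not the wait of any one participant.

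Under Intervention, Postintervention, and Follow-up Surveys: "The 8-week intervention period will begin once the participants complete the baseline assessment and anchoring plan worksheet". No section gives a maximum wait or applies the limit on recent use again.

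Ethics Approval confines the app data to be retrieved to the 8-week study and the 8-week observation period. In the Data Analysis Plan, the covariate vector of Equation 2 lists demographic items and self-reported health, and ends with "baseline meditation habit strength, intrinsic motivation for meditation, and measures of time and risk preferences and the respective coefficients". It has no term for prior meditation or prior app use. The primary outcomes section does provide for a baseline self-report of days with any meditation in the past week, inside or outside the app, but that item is not in the vector.

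**The concern.** The primary outcome is a behaviour that participants can already perform, without restriction, between screening and week 1. They hold a paid subscription and wait for an unstated number of weeks. When the clock starts, some may have stopped using the app and others may be practising regularly, although all passed the same low-use limit at screening. Practice just before the start is a plausible predictor of practice at weeks 8 and 16. If the primary model does not hold it, that variation stays in the error of every arm contrast, and the sample's practice at the start of week 1 is not accounted for in the main result.

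**Working it through.** **1. Timeline.** At screening a participant is 0 to 7 days past purchase, with 0 or 1 day of Calm use in the last week. The wait has no stated length. If it is assumed to be 2 to 6 weeks, the clock starts between day 0 + 14 = 14 and day 7 + 42 = 49 after subscribing.

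**2. What the protocol reports about use in that window** (App-Based Mindfulness Meditation section).
- Mental health apps in general: "open rates declining >80% between days 1 and 30 across all mental health apps".
- Meditation apps: median retention of 4.9% at day 15 and 4.7% at day 30.
- The team's own Calm study: a fall of about 68% in adherence over 16 weeks, with no weekly curve.

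Practice is thus likely to change during the wait. How much it changes in annual Calm subscribers is not documented.

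**3. What the trial holds on practice at the start.**

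| Measure | Obtained? | In Equation 2? |
|---|---|---|
| App use before the start | No, outside the retrieval window | No |
| Self-reported past-week meditation days, baseline | Yes | No |
| Baseline habit strength, intrinsic motivation | Yes | Yes |

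**4. Effect on power.** The plan states power 0.82 for h = 0.43 with 88 per group. With two-sided alpha of 0.05 (assumed, as none is stated):

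Power = Φ(h·√(n/2) − 1.96) = Φ(0.43 × √44 − 1.96) = Φ(0.892) = 0.814.

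This agrees with the stated figure to within one point. The stated h fits 15% against 33% (h = 0.428) rather than 10% against 28% (h = 0.472). That is a separate matter.

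The planning rates (15% at 8 weeks, under 10% at 16 weeks) are counted from subscribing, while study weeks are counted from completion of baseline. To see what the shift does, assume exponential decline through 15% and 10%: the weekly rate is ln(0.15/0.10)/8 = 0.0507, and the control rate at study week 16 is 0.10 × exp(−0.0507 × wait).

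| Assumed lag from subscribing to start | Control rate, study week 16 | Power for +18 points, n = 88 |
|---|---|---|
| 0 weeks | 10.0% | 0.88 |
| 2 weeks | 9.0% | 0.89 |
| 6 weeks | 7.4% | 0.92 |

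The lag does not reduce power for a fixed absolute difference.

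**5. Precision.** For a continuous outcome in a linear model, a covariate with correlation r leaves a fraction 1 − r² of the residual variance: 0.96 at r = 0.2 and 0.75 at r = 0.5. These values of r are assumptions, and the formula does not carry over to this trial's main analysis, for two reasons. The primary model is logistic. It also already contains habit strength and motivation, so only the partial correlation given those terms would count. The documents supply neither that correlation nor the spread of pre-start use.

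**The case against.** The strongest reply is that nothing here threatens validity. Randomisation takes place during the wait and the wait is common to all arms, so the arm contrasts are unbiased. That stands in full.

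A second reply is that the trial is not blind to starting practice. It collects past-week meditation days at baseline, adjusts for habit strength and motivation, and allows baseline moderators. This also stands, and it rules out the reading that the trial has no means of telling people who already meditate from those who do not. It does not put the measure into the primary model. The analysis-of-covariance rule adjusts only for characteristics that differ significantly between groups, which does not secure a prognostic covariate.

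A third reply is that Multimedia Appendix 1, which is not shown, may add covariates or a wider data window. It may, but the article itself states both the retrieval window and the covariate list, and both leave prior use out.

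Four stronger readings are tempting and not supported:
- A reader might take the N/A entries at baseline in Table 2 as proof that the primary outcomes lack a baseline value. The same entries stand at weeks 8 and 16. They mean only that the measure is continuous and not tied to a survey.
- A reader might infer that these participants start after a fall of more than 80% in use. That figure covers mental health apps in general.
- A reader might convert assumed correlations into an equivalent number of extra participants. Step 5 shows why that has no basis here.
- A reader might conclude that the baseline link should go out at randomisation. With use capped below 2 days in the last week at screening, a short wait would remove most of the spread in the proposed covariate.

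**Conclusion.** The point holds as one of efficiency and of describing the starting population. New-user status and low use are fixed at screening, the clock starts after an unspecified number of weeks, and practice in between is neither retrieved from the app nor represented by a direct measure in Equation 2. There is no bias between arms and no loss of power for the 18-point difference; the power illustration rests on an assumed wait of 2 to 6 weeks and an assumed exponential decline. The cost is forgone precision on the arm contrasts, and its size cannot be computed from the documents. That prior practice predicts later adherence is a reasonable expectation, not something the protocol shows. This is an inexpensive improvement, not a flaw that undermines the comparison.

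**What to change.** **Minimum change.** Add the baseline self-report of past-week meditation days to the covariate vector of Equation 2 and to the repeated-measures model. The baseline questionnaires precede the arm-specific video, so the answer is not affected by that content. The item is already collected, so this costs nothing.

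**Preferred addition.** Extend the app-data request back to the subscription date. Pre-specify as a covariate the number of days with at least 10 minutes of meditation in the available days, up to 14, before the baseline link is sent. This uses the same daily definition as the outcome, avoids recall error, and precedes the arm-specific video. The app logs the day, time and length of each session, so the data should already exist with the app company. The cost is a longer date range in the request and consent wording that covers app use back to subscription.
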